## Abstract

**Background:**

Lumbar spinal stenosis is one of the most common causes of low back pain among older adults and can cause significant disability. Despite its prevalence, treatment of spinal stenosis symptoms remains controversial. Epidural steroid injections are used with increasing frequency as a less invasive, potentially safer, and more cost-effective treatment than surgery. However, there is a lack of data to judge the effectiveness and safety of epidural steroid injections for spinal stenosis. We describe our prospective, double-blind, randomized controlled trial that tests the hypothesis that epidural injections with steroids plus local anesthetic are more effective than epidural injections of local anesthetic alone in improving pain and function among older adults with lumbar spinal stenosis.

**Methods:**

We will recruit up to 400 patients with lumbar central canal spinal stenosis from at least 9 clinical sites over 2 years. Patients with spinal instability who require surgical fusion, a history of prior lumbar surgery, or prior epidural steroid injection within the past 6 months are excluded. Participants are randomly assigned to receive either ESI with local anesthetic or the control intervention (epidural injections with local anesthetic alone). Subjects receive up to 2 injections prior to the primary endpoint at 6 weeks, at which time they may choose to crossover to the other intervention.

Participants complete validated, standardized measures of pain, functional disability, and health-related quality of life at baseline and at 3 weeks, 6 weeks, and 3, 6, and 12 months after randomization. The primary outcomes are Roland-Morris Disability Questionnaire and a numerical rating scale measure of pain intensity at 6 weeks. In order to better understand their safety, we also measure cortisol, HbA1c, fasting blood glucose, weight, and blood pressure at baseline, and at 3 and 6 weeks post-injection. We also obtain data on resource utilization and costs to assess cost-effectiveness of epidural steroid injection.

**Discussion:**

This study is the first multi-center, double-blind RCT to evaluate the effectiveness of epidural steroid injections in improving pain and function among older adults with lumbar spinal stenosis. The study will also yield data on the safety and cost-effectiveness of this procedure for older adults.

**Trial Registration:**

Clinicaltrials.gov NCT01238536

## Background

Lumbar spinal stenosis is one of the most common causes of low back pain among older adults and can result insignificant disability [1]. The cause of spinal stenosis is often multifactorial and the clinical presentation can be variable. Degenerative changes in the spine such as spondylosis, facet arthropathy, disc degeneration, and scoliosis may all contribute to the development of spinal stenosis. The symptoms of lumbar spinal stenosis range from low back pain to neurogenic claudication with lower extremity pain, weakness or sensory changes and are often aggravated by walking. Because spinal stenosis can affect the central canal as well as the lateral recesses and intervertebral foramen variably, symptoms can involve single or multiple myotomes and dermatomes. Because the causes of spinal stenosis are most frequently degenerative changes, the symptoms often, but not always, worsen over time. Lumbar spinal stenosis is often associated with poor patient health outcomes and functioning, high resource utilization, and substantial payer, patient, and health-system costs.

Despite the prevalence of symptomatic lumbar spinal stenosis among older adults, treatment remains controversial, with limited comparative effectiveness evidence. Common treatments include conservative measures such as non-steroidal anti-inflammatory drugs (NSAIDS), activity modification, and physical therapy, as well as more invasive treatments such as epidural steroid injections (ESI) and surgery [1]. Although surgery provides some benefit to certain individuals with spinal stenosis [2,3], the results of surgical treatment tend to be modest and may be accompanied by short and long term postoperative surgical complications [4]. Consistent with the general trend of using more minimally- invasive treatment approaches in health care, ESIs are being used with increasing frequency as a less invasive, potentially safer and more cost-effective treatment. However, there is a lack of evidence examining the efficacy, safety, and effectiveness of ESI for symptoms of spinal stenosis. Despite the lack of data demonstrating effectiveness in patients with spinal stenosis, an estimated 25% of all ESIs performed in the Medicare population and 74% of ESIs in the Veterans Affairs system are for spinal stenosis [5,6].

A few cohort studies suggest that ESI may provide short-term pain relief [7,8]. However, the results of RCTs have been less favorable. One early RCT [9] demonstrated no advantage of ESI over saline or local anesthetic injections. However, some argue that the poor results of this trial were a consequence of inadequate technique and do not reflect the current practice of performing ESI with fluoroscopic guidance to ensure appropriate placement of the steroid medication [10].

Only one RCT of fluoroscopically-guided ESI compared to injections with local anesthetic alone has been published [11]. This study, while showing improvement in each group, found no advantage of the steroid injection over an injection of local anesthetic alone [11]. However, this study suffered significant methodological limitations including lack of statistical power, no primary outcome measure, un-blinding of patients and researchers and a high dropout rate (21/60 patients).

The overall objective of this multi-center, double-blind RCT is to evaluate the effectiveness of ESI plus local anesthetic versus local anesthetic alone in improving pain and function among older adults with back pain and lumbar spinal stenosis. We hypothesize that patients randomized to receive ESI with local anesthetic will show significantly greater improvement in pain and function compared to patients randomized to receive local anesthetic only. We will also examine whether ESI is differentially effective in improving pain and function for different patient subgroups (African-Americans vs. Caucasians and patients undergoing a transforaminal vs. interlaminar approach). Finally, we will compare resource use and costs in the two treatment groups as well as incremental cost-effectiveness and incremental cost utility from both payer and societal perspectives.

## Methods/design

### Study design

The Lumbar Epidural steroid injections for Spinal Stenosis (LESS) study is a double-blind RCT of ESI plus local anesthetic injections versus local anesthetic injections for the treatment of pain associated with lumbar spinal stenosis in older adults. Patients, study investigators, and the research staff collecting data will remain blinded to patient treatment allocation.

The patient follow-up has three distinct phases--from randomization and baseline injection to the primary endpoint at six weeks, from optional crossover at six weeks until nine weeks, and the follow-up period from nine weeks to one year after randomization (see Figure 1). Randomization will occur just prior to the first injection. There is a follow-up visit at three weeks from randomization, at which time the participants may have a second injection if they choose, and blood is drawn to obtain cortisol, HbA1c and fasting glucose levels.

**Figure 1 F1:**
[figure not shown]
**Study Flow Chart**.

As an inducement to study enrollment, we will allow crossover after the primary outcome data have been collected at six weeks. Participants may crossover to the other blinded treatment arm if they believe they had insufficient benefit from the first two injections. Also at six weeks, patients will return to discuss potential crossover and to again have blood drawn for cortisol, HbA1c and fasting glucose measures. Those who choose not to crossover at six weeks will be allowed to have one additional injection of the same type as originally assigned at the nine-week time point, if they desire. After nine weeks, patients and physicians will be allowed to make treatment decisions per usual care. This may include ESIs or other treatments as determined by the patient and physician.

### Subjects and setting

The LESS trial is part of a research program to study older adults with back pain, the Back pain Outcomes using Longitudinal Data (BOLD) project. The project involves building a registry designed to capture data from patients enrolled in three large integrated health care systems in the United States. The BOLD registry will provide a mechanism for collecting outcomes data on a large number of patients with back pain and will serve as a portal for entry into studies such as the LESS trial. We will also be recruiting patients from several academic medical centers. Each participating clinical site obtained local Institutional Review Board (IRB) approval prior to subject recruitment. Patients with spinal stenosis referred for an ESI are asked if they would like to participate in the LESS trial. Prior to recruitment, the treating physician determines whether the patient is an appropriate candidate for ESI based on history, physical examination and imaging studies. The physician introduces the study at the end of this consultation if the patient is deemed an appropriate candidate for ESI. Each potential participant is invited to view an educational video that describes the study and provides detailed information about the procedures and implications of participation in the study. Patients provide written informed consent when enrolling in the study.

### Eligibility criteria

Study inclusion and exclusion criteria are listed in Table 1. Inclusion criteria were chosen to include older adults with at least moderate pain and disability related to neurogenic claudication from central spinal stenosis. Subjects will need to have CT or MRI evidence of central lumbar spinal stenosis (mild, moderate or severe) according to the criteria of Boden et al. [12] Patients with lateral recess or foraminal stenosis without the presence of central canal stenosis are not included in this study. The exclusion criteria were chosen for safety concerns as well as to eliminate known confounders that might influence the results of the study or hinder participation and follow-through with study protocol. In addition, we are excluding patients with a history of lumbar fusion or decompression surgery (i.e. laminectomy) as well as interspinous process spacer procedures as this may impact the injection technique as well as outcomes. To ensure that treatment results are not influenced by prior ESI use, we are also excluding patients with a history of lumbar ESI within the last six months.

**Table 1 T1:** Inclusion and Exclusion Criteria

Inclusion Criteria	Exclusion Criteria
Pain in the low back, buttock, and/or lower extremity (pain NRS > 4) with standing, walking and/or spinal extension (buttock/leg > back pain)	Cognitive impairment that renders the patient unable to give informed consent or provide accurate data.
Roland-Morris score of at least 7	Fibromyalgia diagnosis, chronic widespread pain, lower extremity amputation, Parkinson's, head injury, stroke, other neurologic conditions.
Mild-moderate-severe lumbar central canal spinal stenosis identified by MRI or CT according to the criteria of Boden et al. [12]	Severe vascular, pulmonary or coronary artery disease that limits ambulation including recent myocardial infarction (within the last 6 months).
Lower extremity symptoms consistent with neurogenic claudication	Spinal instability requiring surgery.
Must be able to read English and complete the assessment instruments	Severe osteoporosis as defined by multiple compression fractures or a fracture at the same level as the stenosis.
Age 50 or older	Metastatic cancer.
	Excessive alcohol consumption or evidence of non-prescribed or illegal drug use as determined by the TICS screening questionnaire (1 or more positive answer).
	Possible pregnancy or other condition that precludes the use of fluoroscopy.
	Concordant pain with internal rotation of the hip (or known hip joint pathology).
	Active local or systemic infection.
	Allergy to local anesthetic, steroid or contrast.

### Baseline and follow up assessments

Patients with spinal stenosis who are being referred for an ESI as part of their treatment plan are invited to participate in this study by the treating physician. Interested patients are then screened for eligibility by the research coordinator at the site. If eligible, the potential participant is asked to participate in the study and to complete the informed consent process. A study physician reviews each potential participant's imaging studies to determine the eligibility criterion of presence of central spinal canal stenosis and to categorize the stenosis as mild, moderate or severe.

Baseline questionnaires assess demographic, clinical, and disease-history information and include patient self-report measures of pain, function, fear avoidance [13], and pain catastrophizing [14]. We also ask patients at baseline about their preferences for assignment to the ESI versus the control intervention, and to rate their expectations of pain relief. All medications used for pain at baseline are documented by medical record review as well as co-morbidities measured by the Charlson Comorbidity index [15].

Our primary outcomes are measures of function and pain. These include the Roland-Morris Disability Questionnaire, a back pain-specific functional status questionnaire adapted from the generic Sickness Impact Profile (SIP). It consists of 24 yes/no items, which represent common dysfunctions in daily activities experienced by patients with low back pain. The other primary outcome measure is pain recorded on an 11-point numerical rating scale(NRS) measuring average leg and back pain (separately) in the past week. The primary outcome measures are completed at 3 days, 14 days, 3 weeks, 6 weeks, and 3, 6 and 12 months post-randomization.

Secondary outcome measures include the Brief Pain Inventory (BPI) Interference scale [16], the Patient Health Questionnaire (PHQ-8)measure of depression [17], Generalized Anxiety Disorder (GAD-7) measure [18], Swiss Spinal Stenosis Questionnaire (SSSQ) [19-21], and the EQ-5D [22]. These are administered at all follow-up time points with the exception that the SSSQ, BPI, PHQ-8, GAD-7 and EQ-5D are not administered at Days 3 and 14.

At baseline and at three weeks and six weeks post-injection, we draw blood to measure HbA1c and fasting blood glucose and morning blood cortisol levels to monitor for hyperglycemia and adrenal suppression following steroid administration. Because patients are blinded to treatment assignment, these are checked in all patients regardless of treatment received. In addition, at each in-person visit, we check blood pressure and weight because these can also be affected by steroid administration.

Other measures include patient-completed resource utilization questionnaires to collect information on prescription and over-the-counter medication use, medical visits outside the health plan, and other patient burdens and costs during four 3-week periods throughout the 12-month study. Resource use and costs for utilization within each health system are available through the electronic health information systems (pharmacy and medical use).

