### Primary analyses

Our primary analysis will evaluate the effect of ESI + local anesthetic compared to local anesthetic alone using repeated measures analysis of covariance (ANCOVA). Each ANCOVA model will adjust for the respective outcomes measured at baseline and a dummy variable indicating study recruitment site. From the ANCOVA models, we will report on the means and standard deviations of six-week outcome measures for each group and an adjusted estimate of the mean difference (95% CI) between groups. We will adjust the primary analysis for important baseline characteristics that, despite randomization, differ between groups and are associated with the outcomes.

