### Sample size

Our target is to enroll up to 400 patients with half randomized to ESI + local anesthetic and half to local anesthetic alone. We determined overall sample size based on the primary outcome (Roland Morris Disability Questionnaire) with two subgroup analyses (race: Caucasian/non-Caucasian; approach: interlaminar/transforaminal). We will use ANCOVA as the primary method of analysis with the following parameters: 85% follow-up at 6 weeks; two-sided Type 1 error rate of α = 0.05; and adjustment for recruitment site and the outcome measured at baseline. For the purpose of sample size estimation, we conservatively assume six-week Roland Morris Disability Questionnaire scores will have a standard deviation of 7.5 for each group and a correlation between baseline scores and six-week scores of 0.3. For the combined (n = 400) assessment of ESI + local anesthetic vs. local anesthetic alone, the LESS study has 83% power to detect between-group mean differences as small as 2.25 points on the Roland Morris Disability Questionnaire.

Subgroup analyses were powered to detect clinically meaning differences between treatments *within *each subgroup; we did not power the study for the hypothesis of a larger treatment effect within one subgroup compared to another (e.g. an interaction). We adjusted the overall two-sided Type 1 error rate of α = 0.05 using a Bonferroni correction for two tests of the data. Using ANCOVA methods, a sample size of n = 200 (100 per group) provides 83% power to detect between-group mean differences of 3.25 points on Roland Morris Disability Questionnaire.

While formal interim analyses of treatment effect are not planned for this study, we will generate blinded variance estimates for the primary outcomes measured at 6 weeks after a minimum of 100 patients have been enrolled. Conservative estimates of outcome variance and 6-week retention utilized in the initial design of the study yielded an overall upper-bound sample size of n = 400. Adaptive sample size re-estimation will be conducted to provide more precise overall sample size requirements given the observed variance and retention rate, while maintaining the overall Type 1 error rate and power for the stated effect sizes [30].

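### The protocol does not settle whether it has one primary outcome or several, nor which pain score is primary, so its 5% error rate and 83% power describe the Roland-Morris test alone

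*Protocol article*

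**What the plan says.** The places that define the primary outcome do not agree.

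- **Abstract, Methods:** two outcomes. "The primary outcomes are Roland-Morris Disability Questionnaire and a numerical rating scale measure of pain intensity at 6 weeks".
- **Baseline and follow up assessments:** RMDQ, and as the other primary measure "pain recorded on an 11-point numerical rating scale(NRS) measuring average leg and back pain (separately) in the past week". Two pain scores are collected. Neither is designated as the pain primary, and no combination of them is defined.
- **Sample size:** one outcome. "We determined overall sample size based on the primary outcome (Roland Morris Disability Questionnaire) with two subgroup analyses", at two-sided 0.05. The last paragraph of the same section returns to the plural when it plans blinded variance estimates.
- **Background:** the hypothesis is that steroid patients "will show significantly greater improvement in pain and function compared to patients randomized to receive local anesthetic only".
- **Primary analyses:** one model per outcome. "Each ANCOVA model will adjust for the respective outcomes measured at baseline", and each model yields "an adjusted estimate of the mean difference (95% CI) between groups".

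The only multiplicity correction in the article is a Bonferroni adjustment for two tests, in the subgroup paragraph of the sample size section. No section says whether success requires RMDQ alone, either outcome, or both.

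**The concern.** The error rate and power of a trial belong to a claim, and here the claim is not fixed. Suppose steroid injections improve leg pain significantly but not RMDQ. Read from the sample size section, the trial has failed on its primary outcome. Read from the abstract, it has succeeded on one of two. Read from the hypothesis, it has met half of a joint claim. Unless a rule is written down, the choice can be made after the result is known.

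The planned blinded sample size re-estimation depends on the same point. It is meant to preserve the type 1 error and power for the stated effect sizes, but the only effect sizes stated are RMDQ points. Pain has no standard deviation, target difference or power in the article.

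**Working it through.** **Inputs (Sample size section).** 400 enrolled, 1:1, 85% followed to 6 weeks, so 0.85 × 200 = 170 per arm. RMDQ standard deviation 7.5, baseline correlation 0.3, difference 2.25, two-sided alpha 0.05.

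**Step 1: reproduce the plan's figure.**
- ANCOVA standard deviation: 7.5 × √(1 − 0.3²) = 7.155.
- Standard error: 7.155 × √(2/170) = 0.776. Ratio: 2.25/0.776 = 2.90.
- Power: Φ(2.90 − 1.96) = 82.6% (82.4% with the noncentral t). The plan says 83%, so it reproduces.

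**Step 2: does that figure already allow for a second primary outcome?** With the same inputs, power is 74.5% at alpha 0.025 and 69.3% at alpha 0.0167. Even with no loss to follow-up (200 per arm), it is 81.7% at 0.025. The 83% therefore spends all of 0.05 on RMDQ.

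**Step 3: what the figures become under each success rule.** Two assumptions are needed that the protocol does not supply: the correlation between the test statistics (0 to 0.9, equal for all pairs) and, for power, that each pain score has the same 82.6% power as RMDQ. With independent tests, familywise error is 1 − 0.95² = 9.75% for two and 1 − 0.95³ = 14.3% for three. Joint power is 0.826² = 68% and 0.826³ = 56%. The rest come from simulating multivariate normal statistics (4 million draws per setting).

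| Correlation | Any-win error, 2 outcomes | Any-win error, 3 outcomes | All-win power, 2 outcomes | All-win power, 3 outcomes |
|---|---|---|---|---|
| 0 | 9.7% | 14.3% | 68.3% | 56.4% |
| 0.3 | 9.5% | 13.6% | 70.5% | 61.5% |
| 0.5 | 9.1% | 12.6% | 72.4% | 65.3% |
| 0.7 | 8.4% | 10.9% | 74.7% | 69.6% |
| 0.9 | 7.0% | 8.4% | 78.0% | 75.4% |

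The any-win errors count a false finding in either direction, with each outcome tested at two-sided 0.05.

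**Step 4: which stated figure fails under which rule.**
- RMDQ as sole primary: 5% and 83% both stand.
- All must win: 5% holds as an upper bound, and joint power falls below 83%.
- Any win suffices: error exceeds 5%, while the chance of at least one win is 87-97% for two outcomes and 89-99% for three.

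**Step 5: cost of plain Bonferroni.** To hold 83% for RMDQ, 207 per arm are needed at 0.025 (414/0.85, about 488 enrolled) or 227 at 0.0167 (454/0.85, about 535). Both exceed the ceiling of 400.

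**The case against.** This is a condensed article and the analysis plan is not shown. Splitting alpha among named primaries is commonly left to that plan, and sizing a trial on one of two primaries is ordinary practice. Both points are fair: a missing alpha allocation would not by itself be a finding. What remains is a contradiction within the article about how many primary outcomes there are, together with a pain outcome that could be either of two scores. The reference to plural outcomes in the blinded variance estimates shows that pain was not forgotten, but it supplies no pain effect size.

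Four stronger readings are tempting and are not supported.

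- *That the plan allots 0.05 to each outcome.* It never says so. The 0.05 is given for the RMDQ calculation, and equal use for pain is inferred from the 95% interval in each model.
- *That there are three primary outcomes.* The assessments section speaks of pain as one other primary measure. Separate recording of leg and back pain makes three a possible reading only.
- *That neither the 5% nor the 83% holds.* No single success rule breaks both. The inflated error and the reduced power in the table belong to mutually exclusive rules.
- *That RMDQ followed by leg pain is the only scheme that keeps 83% for RMDQ.* Any sequence that starts with RMDQ keeps it, as does naming RMDQ the sole primary.

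**Conclusion.** The concern holds as an internal inconsistency with consequences for inference. The stated 5% and 83% are correct for the RMDQ test. For the claim about pain and function, both are undefined until the pain score and the success rule are fixed.

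Depending on the rule, the gap is either a familywise error of about 7-10% (two outcomes) or 8-14% (three), or a joint power of about 68-78% (two) or 56-75% (three). The error range rests on testing each outcome at 0.05 and on the assumed correlations. The power range rests also on equal marginal power for pain. The inconsistency itself rests on no assumption.

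**What to change.** Before unblinding, make three changes of wording in the protocol and the analysis plan.

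1. Name one pain score at 6 weeks as the pain primary and make the other secondary. Leg pain fits the inclusion criterion in Table 1 that buttock or leg pain exceed back pain. The choice is the sponsor's, and the background also describes the population by its back pain.
2. State a fixed sequence: RMDQ at 6 weeks at two-sided 0.05, then the named pain score at 0.05 only if RMDQ is significant. This holds the familywise error at 5% and leaves RMDQ power as stated. Naming RMDQ the sole primary, with pain secondary throughout, would also keep both stated figures.
3. Say in the sample size section that the 83% applies to RMDQ only.

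No extra patients are needed. The price is that no confirmatory pain claim is possible if RMDQ is not significant. Under the sequence, the power to claim pain as well is the two-outcome joint power above, about 68-78% on the same assumptions.
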